## Abstract

**Introduction:**

Several potentially modifiable factors are associated with the risk of cognitive decline and dementia, indicating potential for risk reduction via lifestyle modifications. While multidomain interventions targeting lifestyle changes for dementia risk reduction are often highly selective and resource-intensive, eHealth/mHealth interventions offer a potentially low-cost, scalable approach to promote brain-healthy lifestyles for a large number of individuals. This protocol outlines a pilot study to test an mHealth intervention for dementia risk reduction among middle-aged to older adults in Germany.

**Methods and analysis:**

We will translate and adapt the smartphone-based intervention MyBraincoach for dementia risk reduction, developed at Maastricht University in the Netherlands, to the German healthcare setting and test the app in a 12-week, non-randomised pre-post pilot study. Key feasibility outcomes include feasibility and success of recruitment, use and usability of the app. Exploratory outcomes include changes in dementia risk profiles, dementia literacy, health-related quality of life, self-efficacy and motivation for behaviour change. A sample of n=75 adults aged 40–75 years will be recruited across Germany, using diversified convenience sampling. Data will be collected using web-based questionnaires at baseline and follow-up after 12 weeks. Feasibility and success of recruitment, including recruitment rates and sample characteristics, will be evaluated descriptively. Changes in dementia risk profiles and other secondary outcomes will be investigated using dependent-samples t-tests and McNemar’s tests as appropriate. Lastly, a moderated remote focus group will be conducted with n=8 participants of the pilot study to gain insights on the target group’s experiences with usage of the app and to assess suggestions for modification and improvement. Respective data will be analysed using structured content analysis.

**Ethics and dissemination:**

Ethical approval was obtained from the Ethics Committee of the Medical Faculty of Leipzig University (ref.: 476/22-ek). Findings will be disseminated via peer-reviewed publications, presentation at (inter)national scientific conferences and social media channels, respectively. Results will inform design and sample size of a confirmatory randomised controlled trial to assess effectiveness of the intervention.

**Trial registration number:**

German Clinical Trials Register (DRKS00038349).

Strengths and limitations of this studyInternet-based interventions constitute an innovative, accessible approach for delivering tailored advice on brain health, possibly able to reach large parts of society and allowing for large-scale implementation.We will test an evidence-based mHealth tool in German adults aged 40–75 years, targeting dementia risk reduction and brain health based on a validated dementia risk score.Using both quantitative and qualitative methods, we will provide insights on the feasibility of recruitment, use, usage patterns and usefulness of the app, as well as users’ perspectives, enhancing involvement of the target group.Recruiting diverse samples, including, for example, adults with lower socioeconomic backgrounds, is challenging in lifestyle interventions, and use of eHealth tools is generally lower in socioeconomically disadvantaged populations, complicating inclusive study sampling.Participants will be included irrespective of their baseline dementia risk to enhance the applicability of the findings to the general population, which may limit detectable changes in dementia risk profiles due to potential floor effects.

## Introduction

 The number of people living with dementia is increasing globally, particularly due to population ageing, with cases expected to triple from an estimated 55 million in 2019 to 152 million in 2050.^1^ Despite recent advances in disease-modifying treatments,^2
3^ their clinical indication is narrow and a readily available cure is currently not on the horizon. A vast amount of research indicates possibilities for dementia risk reduction by modification of risk factors. Established risk factors include, for example, hypertension, diabetes mellitus, physical inactivity, hearing loss, social isolation, smoking or depression.^4^ Further evidence is accumulating for other individual-level and population-level risk and protective factors.^5^

Evidence on lifestyle-based risk factors for dementia has resulted in the launch of numerous randomised controlled trials (RCTs), assessing the effects of lifestyle modifications on cognitive performance and further outcomes, for example, dementia risk scores, in at-risk populations. Particularly, multidomain interventions targeting several risk factors simultaneously have been suggested as promising. The Finnish Geriatric Intervention Study to Prevent Cognitive Decline and Disability (FINGER) reported small but significant effects of an intensive 2-year multidomain lifestyle intervention on cognitive performance in older (60–77 years) adults at increased risk for dementia.^6^ Currently, several studies, organised in the World-Wide-FINGERS-network, are adapting this approach to different regional and cultural settings as well as target populations globally.^7^ Findings of completed trials are mixed, with some interventions showing positive effects on cognitive performance,^8–10^ while others report negative results.^11–13^ However, respective interventions are often resource-intensive and highly selective, targeting older high-risk populations rather late in life (>70 years), therefore benefiting only small parts of society. Evidence suggests that the adverse effects of risk factors on cognitive function seem to increase with ageing,^14^ and many modifiable risk factors for dementia are already highly prevalent among younger populations (40–60 years).^15^ Calls are being made to address dementia risk reduction and brain health earlier in life, using scalable, accessible means to maximise effects on a population level.^16
17^

The recently updated WHO guidelines on risk reduction of cognitive decline and dementia emphasise the potential of tailored multidomain interventions across the life course, targeting several risk factors for dementia simultaneously. This includes interventions targeting depression, sleep, hearing loss and social isolation. The WHO further emphasises the need for culturally tailored and context-specific interventions, delivered in-person or digitally, to increase accessibility and reach.^18^ To date, implementation research addressing feasibility and scalability of respective interventions remains limited.

Internet-based (eHealth) or mobile (mHealth) interventions have been highlighted as an innovative, accessible and potentially cost-effective approach to provide tailored advice on brain health, allowing for large-scale implementation of highly individualised interventions. Respective interventions might further be useful to raise awareness about brain health, as evidence suggests that knowledge of several risk factors for cognitive decline and dementia, particularly cardiovascular and metabolic risk factors, is limited among the general population.^19–24^ A meta-analysis reported small to moderate effects of eHealth interventions on cognitive performance and dementia risk scores.^25^ Recent findings from the Australian Maintain Your Brain-trial further reported beneficial effects of a personalised digital intervention on cognitive performance, a validated dementia risk score and several lifestyle factors, including diet, physical activity and psychological distress at 3-year follow-up.^9^ Several respective eHealth/mHealth interventions for primary or secondary prevention of dementia, daily life support, screening and decision making have been developed and evaluated recently, aiming to support primary or secondary prevention, screening, decision making or support in daily life, with most interventions in the stage of early evaluation and maturity.^26^ Dementia risk reduction using eHealth/mHealth interventions in primary care/general practitioner (GP) settings have proven feasible in several studies,^27
28^ further suggesting potential for implementation on a scalable level. However, it remains unclear whether a culturally tailored multidomain mHealth intervention can be successfully implemented and accepted in a German population.

Against this background, we aim to test a translated and adapted version of an evidence-based mHealth intervention for dementia risk reduction, the MyBraincoach-app,^29^ in a pre-post pilot study among German adults aged 40–75 years. Feasibility and acceptability will be evaluated in terms of:

Feasibility of recruitment.Success rate of retention of participants at 12 weeks follow-up assessment.Usage (patterns) of the app.Perceived use and usability of the app.Reasons for non-use and study dropout.

Further exploratory objectives are:

To investigate change in knowledge of risk and protective factors for dementia.To describe changes in dementia risk profiles at 12 weeks follow-up.To assess changes in self-efficacy, motivation for behaviour change and health-related quality of life.To gain exploratory insights into participants’ perception of the app by means of a moderated focus group.

A proof-of-concept-study in community-dwelling middle-aged adults in the Netherlands investigated usage patterns and appreciation of the Dutch app (V.1.0), as well as changes in knowledge and attitudes towards dementia risk reduction.^29^ While overall app use was modest (56%), those who used the app evaluated it positively, increased their knowledge on dementia risk reduction and showed more positive beliefs about health behaviour change at follow-up. In a further proof-of-concept-study testing the app in Dutch primary care patients (n=188), 69.2% of users considered the app useful.^28^ The app improved knowledge on dementia risk reduction, while dementia risk improved in both the intervention (GP consultation+app) and control group (GP consultation only).

The present study aims to provide context-specific evidence on recruitment and retention, patterns of app engagement, perceived usefulness and usability and accessibility of an adapted version of the app in a German setting. By combining a quantitative feasibility assessment with qualitative user feedback, it will provide implementation knowledge required to refine the intervention and inform the design of a subsequent RCT.

## Methods and analysis

### Study design

We will conduct a non-randomised pre-post pilot study to test the translated and adapted MyBraincoach-app among n=75 middle-aged and older adults in Germany. The pilot study will be conducted in accordance with the extended Consolidated Standards of Reporting Trials (CONSORT) statement for feasibility and pilot trials.^30^ Further, to gain a better understanding of user experiences and potential suggestions for improvement, a moderated, video-based focus group will be conducted with n=8 participants following completion of the pilot study. These findings will inform the decision to conduct a subsequent confirmatory RCT to investigate intervention effectiveness.

### Participants

Eligible for the study will be individuals aged 40–75 years, recruited nationwide in Germany, with internet access by use of a smartphone with internet connection and sufficient command of the German language. Recruitment is planned to commence on 1 November 2026 and, following rolling enrolment and individual 12-week intervention periods, is anticipated to be completed after the final follow-up assessment and focus group by 30 June 2027. Individuals with a dementia diagnosis or severe conditions possibly interfering with safe use of the app will be excluded from participation. Participants will provide information on current diagnoses using a custom self-report questionnaire. Further exclusion criteria include current participation in other studies testing healthy ageing interventions. No minimum number of modifiable risk factors will be required for study participation, and individuals with few or no risk factors will remain eligible, as the intervention also aims at improving knowledge about the links between lifestyle and brain health and reinforce the maintenance of protective health behaviours.

### Recruitment

Participants will be recruited primarily online using convenience sampling. To mitigate the risk of recruiting a predominantly highly educated and health-literate sample, a broad and diversified recruitment strategy will be employed. Recruitment channels will include advertisements in health-related and general-interest online forums and magazines, community newsletters, volunteer registries, social media channels of Leipzig University and other research institutions or non-governmental organizations, as well as community health centres and GP practices. Additional recruitment efforts will target platforms and settings with broader sociodemographic reach. Interested individuals will click on a link leading to the study homepage, where they will be able to sign an online informed consent form and provide their contact information. Eligible participants will then receive a personalised QR-code via email to download the app to avoid non-participants downloading the app, as well as a link to the baseline assessment to complete online. Questionnaire data and app metadata will be linked via a unique pseudonymised study ID embedded in the personalised survey links and stored in the app at first login. Participants will be reimbursed with 20€ for their efforts.

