### Study procedures

After signing the informed consent form, participants will complete the baseline assessment, comprising standardised questionnaires on sociodemographic factors, health-related quality of life, self-efficacy, motivation for behaviour change and knowledge about risk/protective factors for dementia (see ‘Outcomes and measures’ section). A reminder will be sent per email to those having consented but did not complete the baseline assessment after 2 weeks. If no baseline data are submitted after this reminder, only the signed consent and minimal contact information will be retained for documentation purposes, and no other personal data will be processed. Consenting participants will then be able to download the MyBraincoach-app. All participants will receive a reminder via email 2 weeks after enrolment in the study to encourage download and use of the app.

At the end of the intervention period (12 weeks), all participants will receive an email with a link to the follow-up assessment, containing the same questionnaires as used at baseline, as well as assessing perceived use and usability of the app. During the follow-up assessment, participants can provide consent to be re-contacted for participation in the video-based focus group. A remote focus group with an expected duration of 90–120 min will then be scheduled, including n=8 pilot study participants, moderated by a researcher experienced in qualitative methodology. Participants will be purposively selected from those consenting to be re-contacted. Subject to participant availability, selection will aim to include individuals with different levels of app engagement, varied educational and sex backgrounds.

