### Data management

Information necessary to assess success and feasibility of recruitment will be assessed by the research team at the study centre, using standardised custom-made forms. Download and use of the app, including information on specific app features and number of interactions with the app, will be assessed using meta-data, provided by the web-design agency Indicia Betawerk, responsible for development and hosting of the app. Baseline and follow-up assessments will be conducted online using Limesurvey software. Secured hyperlinks to the baseline and follow-up assessment will be sent via email to all individuals who provided online informed consent to participate.

Safeguards will be implemented to prevent unauthorised changes of data (passwords, access rights), and only researchers entrusted with data handling, reimbursement of participants and analyses within the project will have access to the data. Source documents and data management procedures will be maintained readily available. Quality of data (eg, data from online assessments, documents regarding study and participant management, etc) will be monitored continuously. Data protection laws, such as the European General Data Protection Regulation, will be followed and every person having or requesting access to the data is obliged to confidentiality. All personal information of participants will only be documented for the duration of the study and will be saved separately from meta-data and data collected at the baseline and follow-up assessments, complying with data protection laws. Account data needed for reimbursement of participants will be deleted immediately on completion of reimbursement. Personal identification data of participants will be saved on a central server restricted by password access after assigning a randomised pseudonym ID to each participant. All analyses conducted within the project will solely use de-identified, pseudonymised data.

Meta-data, for example, on number of app downloads, logins and interactions with the app, are stored on a secured server in the Netherlands. Data are transferred using a Secure Sockets Layer certificate and will only be stored in a pseudonymised fashion to ensure participant anonymity. On signing the informed consent, participants will further be informed of the modes and purposes of data collection, storage and usage, as well as their rights to demand correction or deletion of their data.

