### Data analysis plan

#### Quantitative analyses

All acquired data will be examined for potential inconsistencies and missing values. Drop-out analyses will assess potential systematic biases between participants who complete the follow-up assessment 12 weeks after baseline and non-completers, using χ² and two-sample t-tests, as appropriate. Success and feasibility of recruitment, retention of participants, use and usability of the app as well as reasons for dropouts will be described using means (SDs) and percentages, as appropriate. Changes in LIBRA, dementia literacy, health-related quality of life, self-efficacy and motivation for behaviour change will be described using dependent samples t-tests. The significance level of all analyses will be set to p<0.05 (two-tailed). Analyses will be conducted using Stata/SE V.16.0. Results will be reported according to the extended guidelines of the CONSORT statement for pilot and feasibility trials.^30^

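### The Recruitment and Study procedures sections disagree on whether app access comes after baseline, and neither makes it depend on a submitted baseline

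*Protocol article*

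**What the plan says.** The protocol article describes the participant flow in two places.

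- **Recruitment.** After online consent, eligible participants are emailed a personal QR-code "to download the app to avoid non-participants downloading the app, as well as a link to the baseline assessment to complete online". The only purpose given for the personalised code is to keep non-participants out. Survey and app records are linked by a study ID that is stored in the app at first login.
- **Study procedures.** "After signing the informed consent form, participants will complete the baseline assessment". People who have consented but have not completed baseline are reminded after two weeks. If baseline is still missing after that, only consent and contact details are kept. The text continues: "Consenting participants will then be able to download the MyBraincoach-app". It then adds: "All participants will receive a reminder via email 2 weeks after enrolment in the study to encourage download and use of the app".

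Under Intervention, the first step of app use is the LIBRA assessment, which produces a personal risk profile. The user then chooses a topic and receives daily notifications on it for 14 days. The advised period of use is 12 weeks. Under Quantitative analyses, changes in LIBRA, dementia literacy, quality of life, self-efficacy and motivation are examined with dependent-samples t-tests. Outcomes and measures classes the change outcomes as exploratory and the recruitment, retention, use, usability and dropout measures as key feasibility outcomes.

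**The concern.** In a pre-post study without a control group, the change score can be read only if the pre measurement precedes the intervention. The Recruitment section puts the app in the participant's hands at the same step as the baseline link. The Study procedures section suggests baseline first, but the condition it attaches to the download is consent. No section describes a technical lock, an instruction to finish the survey first, or a rule for a baseline that arrives after first login.

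The content of the app makes the order matter. Its stated aim is to improve knowledge and motivation, and both are measured at baseline. A participant who opens the app first has already seen risk feedback, and perhaps several teaching messages, when answering the baseline questions. With no comparison group, the outcome data would not show that this had happened. The abstract says the results will inform the design and sample size of a randomised trial, so understated changes could be carried into that planning.

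**Working it through.** **1. The two accounts side by side**

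- Order of baseline and app: Recruitment gives none, since code and link are listed together. Study procedures gives baseline, then app, by narration.
- Condition for the app: Recruitment says eligible, after consent. Study procedures says consenting. A submitted baseline is a condition in neither.
- App-use reminder: addressed to all participants, two weeks after enrolment, with no stated exception for those whose baseline is outstanding.

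A site that follows the Recruitment text could send both items together and still satisfy the literal wording of Study procedures, because every recipient has consented.

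**2. Possible exposure before baseline**

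Inputs: baseline reminder at 2 weeks (Study procedures); 12 weeks of use and 14 days of notifications per topic (Intervention).

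- Intervention length: 12 × 7 = 84 days.
- App use possible before the baseline reminder: 14 days.
- Share: 14/84 = 16.7%, about 17%.

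This assumes a download on the first day and a reminder clock that starts when the code is received. Fourteen days would fit one topic only if each notification is opened daily, because unopened content is held over to the next day. A baseline submitted after the reminder could follow longer use.

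**3. How the bias would scale**

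Let f be the share of analysed participants who use the app before baseline, and g the share of the eventual effect already present when they answer. If the true change is the same in early and late users, then

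observed mean change = true mean change × (1 − f × g).

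The document gives neither f nor g, so the following values are assumptions that show the range:

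- f = 10%, g = 1/6: 1 − 0.017 = 98% of the change retained.
- f = 25%, g = 1/6: 1 − 0.042 = 96%.
- f = 50%, g = 1/6: 1 − 0.083 = 92%.
- f = 25%, g = 1/2: 1 − 0.125 = 88%.
- f = 50%, g = 1/2: 1 − 0.25 = 75%.
- f = 50%, g = 1: 1 − 0.50 = 50%, conceivable only for something learnt quickly, such as literacy.

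Taking g = 1/6 makes gain proportional to exposure time. The spread from 98% to 50% shows that the result depends on the assumed inputs.

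**4. Link to the planned sample**

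The plan's figure reproduces: 75 × (1 − 0.20) = 60 at follow-up. Leaving early users out of the paired analyses would remove 6 of 60 at f = 10% and 15 of 60 at f = 25%. The planned size itself is not affected by this point.

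**The case against.** The strongest reply is that Study procedures is the section that sets the sequence, and its natural reading is baseline before app. On that view the Recruitment sentence is merely compressed, and the trigger that releases the code is operational detail a journal article leaves to the full protocol. Part of this stands: the intended order is probably baseline first. But the article does state the flow, states it in two ways, and names consent as the condition where it could have named baseline.

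A reader might also infer several stronger things that the document does not support.

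- *That code and link travel in one email.* This is plausible but not stated. The text puts them in one step.
- *That every pre-post change is contaminated.* Only people who log in before submitting baseline are affected. Outcomes and measures says chronic conditions in LIBRA are not expected to resolve within 12 weeks.
- *That the bias must be toward zero.* This requires an early beneficial effect. The Adverse events section allows that risk feedback may raise concern.
- *That Data management adds a third access rule.* "Secured hyperlinks to the baseline and follow-up assessment will be sent via email to all individuals who provided online informed consent to participate" concerns survey links, not the app.
- *That the 12 weeks are counted from conflicting starting points.* Enrolment anchors the two-week app reminder, not the 12 weeks. The follow-up described as being for "participants who complete the follow-up assessment 12 weeks after baseline and non-completers" agrees with a 12-week intervention period if the app follows baseline.
- *That both two-week emails certainly reach people with baseline outstanding on the same day.* Enrolment is not defined, so this is possible but not established.
- *That a definite attenuation such as 10–20% can be quoted.* It would rest wholly on assumed inputs.
- *That data from app users who never submit baseline contradict the plan.* The retention rule in Study procedures already addresses such people.

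Finally, the article says the study is not designed to assess effectiveness. That limits the severity but does not remove the inconsistency.

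**Conclusion.** The point holds in a limited form. The Recruitment and Study procedures sections do not agree on the sequence, and neither makes app access depend on a submitted baseline. Followed as written, the plan lets some participants receive their LIBRA profile and teaching content before the pre measurement. For those participants, and provided the app has an early beneficial effect, change is biased toward zero, mainly in dementia literacy, motivation, self-efficacy and self-reported behaviour.

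The size cannot be determined from the document. What can be said is that about 17% of the intervention period fits before the baseline reminder, on the timing assumptions given. Recruitment, retention, app use, usability, usefulness and reasons for dropout are not pre-post contrasts and are not biased in this way. Severity is moderate, because the affected outcomes are exploratory.

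**What to change.** - Reconcile Recruitment and Study procedures to one sequence: consent and eligibility, then baseline submission, then QR-code.
- Release the QR-code only once the baseline survey has been submitted, by an automatic trigger.
- Send the app-use reminder only to those who have completed baseline.
- Count the 12 weeks from baseline submission and release of the code.
- As a check, compare baseline submission time with first app login through the study ID, and repeat the paired analyses without anyone whose login came first. The article does not list login times explicitly among the metadata, so confirm that the app host will supply them.

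The cost is an email trigger and a few sentences, best settled before recruitment opens. The downside is a slightly longer path to the app and possibly a few more early losses, which are themselves feasibility data. Prevention is preferable to later exclusion, which would shrink the expected 60 analysable participants.
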